
**Figure 4 F4:**
[figure not shown]
**Possible scenarios of observed treatment differences [adapted from **[22]**]**. Shaded area indicates non-inferiority margin.

In the event that women experience no relief from the single injection and request the four injection technique, these women will remain within the study, and the data will be analysed according to ITT and per protocol principles.

Women requesting a repeat injection will receive the standard four injection technique. A pre-injection VAS score will be sought prior to administration and post injection VAS score will be collected at 30 minutes. These will be reported separately.

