### Sample size

A sample size of 133 in each group will be required to achieve 90% power to detect non-inferiority using a one-sided, two-sample t-test. The significance (alpha) of the test is 0.025. The non-inferiority margin is ≤ 1 cm on the VAS and the true difference between the means is assumed to be zero (cms). A standard deviation (SD) of ± 2.5 on the VAS was conservatively estimated from results reported in a recent meta-analysis [6] of SWI studies. As consent and randomisation will occur in the birth suite, attrition is expected to be minimal. However, we have estimated a 20% attrition to account for cases of precipitate birth prior to the assessment of the primary outcome, or other unforseen reasons for withdrawal such as emergency caesarean section. Thus a total of 319 participants will be required.

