### Statistical analysis

Demographic and other baseline characteristics will be analysed for comparability between groups to assess the adequacy of randomisation. Differences in VAS pain score between the two groups will be analysed using Student's t-test and analysis of variance (non-parametric tests used if data is highly clustered toward extremes). Data analysis for the primary outcome will determine if the treatment effect lies within the a priori defined non-inferiority margin (± 1 cm) and the null effect (0 cm) at a one-sided alpha of 0.025. The pre-specified non-inferiority margin was based on a one cm (95% CI 0.6-1.4 cm) minimally clinically significant difference reported for VAS in severe pain [14]. The Mann-Whitney U test will be utilised for non-parametric data and chi-squared test for categorical variables. Women who give birth or elect for narcotic and/or regional analgesia after the collection of the primary measure (VAS score 30 minutes post injection) but before the completion of the secondary outcomes (VAS up to 120 mins) will be included in the trial. Women giving birth or electing for narcotic and/or regional anaesthesia prior to the collection of the primary outcome measure will be included in the Intention to Treat (ITT) analysis. The conservative nature of ITT may obscure differences between treatments groups therefore increasing the chance of falsely declaring equivalence [19]. To address this, some authors have recommended that Per Protocol (PP) analysis also be conducted alongside ITT to provide a more robust conclusion if both methods support the non-inferiority [9,20]. Other authors [21] argue that the benefits of ITT analysis continue to outweigh the PP approach. As it is unlikely that participants in this trial will cross from one intervention to another, the ITT approach will be used unless the dropout out rate exceeds the estimated margin allowed of 20%. Should the dropout rate exceed 20% then a PP analysis will also be conducted. Figure 4 outlines possible scenarios for the outcome of the data analysis based on the pre-defined noninferiority margin, indicated as the shaded area. Error bars indicate 90% confidence intervals (CI). If the CI is completely to the left of zero, the treatment is inferior (scenario A). Scenarios C,D and E indicate noninferiority as the CI lies within the specified margin (shaded area). Scenario F would indicate superiority. An inconclusive result (scenario B) is unlikely as the sample size is sufficiently powered to provide a result [22].

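### Single-injection women re-treated with the four-injection comparator stay in their arm under ITT, and the plan contradicts itself on whether a per-protocol analysis accompanies it

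*Protocol article*

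**What the plan says.** The primary outcome is the fall in VAS pain at 30 minutes (Primary outcome). Scores at 10, 60, 90 and 120 minutes are secondary. The Background describes relief as starting nearly at once and lasting up to two hours.

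The text after Figure 4 sets the re-treatment rule. "In the event that women experience no relief from the single injection and request the four injection technique, these women will remain within the study"; the sentence ends by saying that their data are to be analysed on both ITT and per-protocol principles. It continues: "Women requesting a repeat injection will receive the standard four injection technique". A VAS is sought before the repeat and another 30 minutes after it, and these are to be reported separately.

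The Statistical analysis section chooses the analysis set on this ground: "As it is unlikely that participants in this trial will cross from one intervention to another". ITT is therefore used, with a per-protocol analysis added only if dropout exceeds 20%. The same section concedes that ITT can raise the chance of a false claim of equivalence. The Abstract announces ITT and per-protocol analyses with no condition.

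**The concern.** In the single-injection arm every repeat is a move to the comparator. Nothing in the article limits a repeat to the period after the 30-minute score, and nothing says which value is the primary one if the repeat comes earlier. If observed scores are used as they stand, part of the new arm's result can be the comparator's effect. The women affected are those for whom the single injection did not work. The 60 to 120 minute scores, which bear on the stated aim of comparing duration of relief, leave more time for this to happen.

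In a non-inferiority trial, movement of the two arms toward each other favours the claim under test. The safeguard would be a second analysis set, but the plan disagrees with itself on whether that set is analysed. Its trigger is dropout, and women who are re-treated and remain in the study are not dropouts.

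**Working it through.** **The plan's own figure.** The Sample size section gives: "A sample size of 133 in each group will be required to achieve 90% power"; "The significance (alpha) of the test is 0.025"; "The non-inferiority margin is ≤ 1 cm on the VAS". It assumes a true difference of zero and an SD of 2.5 cm.

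- Normal approximation: n = 2 × 2.5² × (1.960 + 1.282)² / 1² ≈ 131.3, so 132 per arm.
- Noncentral t: 133 per arm, power 0.9015. The stated 133 reproduces.
- Total: 2 × 133 × 1.2 = 319.2, which matches the stated 319.

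**The per-protocol trigger.** 20% of 319 is 63.8, so at least 64 women would have to drop out before the Statistical analysis section calls for per-protocol. Crossovers who stay in the study do not count toward that number.

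**Effect of re-treatment before 30 minutes.**

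- SE of the difference = 2.5 × √(2/133) = 0.3066 cm.
- Let f be the fraction re-treated before 30 minutes and g their mean gain at 30 minutes. The net shift is s = f(single) × g(single) − f(control) × g(control).
- At a true deficit of 1 cm the expected as-observed difference is 1 − s.
- P(declare non-inferior) = Φ(s / 0.3066 − 1.960).

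The documents give neither f nor g. The rows below are assumptions, with s read as the net shift after any control-arm repeats:

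| Crossing | Gain (cm) | s (cm) | P(declare non-inferior) |
|---|---|---|---|
| none before 30 min | – | 0 | 0.025 |
| 2% | 2 | 0.04 | 0.034 |
| 5% | 2 | 0.10 | 0.051 |
| 10% | 2 | 0.20 | 0.096 |
| 10% | 3 | 0.30 | 0.163 |

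Control-arm repeats matter. If 10% of the single arm and 5% of the control arm were re-treated early, each gaining 2 cm, s = 0.20 − 0.10 = 0.10 and the rate is 0.051, not 0.096. Equal rates and gains give s = 0 and no bias from this source.

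The calculation keeps the SD at 2.5 cm and uses the stated one-sided 0.025.

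**The case against.** Five points can be made for the plan.

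1. **Per-protocol is named for these very women.** True: the sentence on crossovers ends with both principles, so a reader who infers that the plan offers ITT alone has stopped too early. What stands is that the Statistical analysis section makes per-protocol conditional on dropout, which conflicts with that sentence and with the Abstract.

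2. **Repeat scores are reported separately.** This covers the repeat's own before and after values. It could be read as taking later scores out of the original schedule, but it does not say so. It is therefore not established that contaminated scores will enter the primary comparison, only that the text permits it.

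3. **Repeats are open to both arms.** Correct. A reader might infer that only the new arm is rescued, or that crossing is the default. Neither is supported: four injections is the rule for any repeat, in either arm, and the plan's view that crossing is improbable is a statement about frequency. The bias depends on the difference between arms. If the single injection is truly worse, more re-treatment in that arm is the natural expectation.

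4. **The size is unknown.** Also correct. One could assume 20% crossing with a 3 cm gain and reach 50% false non-inferiority, but nothing in the documents supports those inputs. An almost immediate onset shows that early requests are possible, not that they are common.

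5. **As-observed ITT may be the intended target.** Women who take narcotic or regional analgesia before 30 minutes are also kept in ITT, so a treatment-policy reading is coherent. That is a fair reason not to make a pre-repeat score the sole primary value. It does not remove the need for a companion analysis when the re-treatment is the comparator itself.

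**Conclusion.** The point holds as a conditional bias combined with an internal contradiction. Followed as written, as-observed ITT can carry the comparator's effect into the single-injection arm and pull the result toward non-inferiority, to the extent that early re-treatment is more frequent or more beneficial there than in the control arm. The Statistical analysis section's ground for ITT and its dropout trigger do not fit the re-treatment rule or the Abstract.

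Under the assumed net shifts, with 133 per arm and SD 2.5 cm, false non-inferiority at a true 1 cm deficit is about 3% to 16% against a nominal 2.5%; 5% crossing with a 2 cm gain about doubles it. If all repeats follow the 30-minute score, the primary outcome is unaffected and only the later scores are exposed.

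**What to change.** Change the analysis wording only; the clinical rule on repeats stays as it is.

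- Reconcile the Abstract, the Statistical analysis section and the text after Figure 4 so that per-protocol is run alongside ITT whatever the dropout rate. Class any woman in either arm who has a repeat injection before 30 minutes as a per-protocol deviation.
- Pre-specify a further analysis in which the pre-repeat VAS, already to be collected, is her value at the next scheduled time point and all later ones, in either arm. Report it beside the as-observed ITT result and require non-inferiority in both. Per-protocol alone would not be enough, because excluding early repeats removes women for whom the single injection failed.
- Remove the statement that crossing is improbable as the ground for relying on ITT alone.

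The cost is about a paragraph of text and a little more analysis, with no new data. The drawback is that carrying a pre-repeat score forward is a simple imputation and somewhat conservative for the single injection, which is why it accompanies as-observed ITT and does not replace it. The wording should be settled before outcome data are seen, since the choice of value could decide the conclusion.

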### Confidentiality and data security

The data is de-identified, coded and entered onto a password protected database.

### Data safety monitoring board

A Data Safety Monitoring Board has not been established for this trial. As there have been no adverse events reported in any previous trial on the topic, the trial was considered to be low risk. However, a senior obstetrician at both sites has agreed to act as a clinical monitor to investigate any adverse events that may be associated with the trial. This process has been approved by the Human Research Ethics Committee at each site.

### Project management

Project management will be overseen by the research team that consists of midwifery and obstetric clinicians, midwifery academics and researchers from both sites. The research team will meet regularly during the projects development phase and regular contact and progress reports maintained via email during the recruitment phase of the trial.

### Ethical issues

Human Research Ethics Committee (HREC) Approval

Mater Health Services HREC   No:1422M

Australian Catholic University HREC   No:Q2009 48

Royal Brisbane and Women's Hospital HREC   No:HREC/10/QRBW/155

#### Women of Non-English Speaking Backgrounds (NESB) and minors

At both sites, an onsite interpreter service is available during "office hours" for the most common language groups of Vietnamese and Mandarin/Cantonese with contract interpreters for eighteen other languages available. At other times the Birth Suite accesses a telephone interpreter service. For NESB women considering SWI as an intervention for back pain, the interpreter service accessed at the time will be utilised to provide information and gain consent for inclusion in the trial. To supplement this, copies of the Participant Information Sheet and consent form will be available in Vietnamese and Mandarin/Cantonese. In the event that a suitable interpreter cannot be found, inclusion in the trial will not be offered. Postnatal data will be collected using this method as interpreters are required when providing routine postnatal information.

#### Potential risks

The four injection SWI technique is routinely used in the birth suites at Site One. Therefore, no additional risks from study participation would be expected. Moreover, no allergic or systemic reactions to the procedure have been reported in the literature other than the brief stinging sensation immediately following administration [5].

## Discussion

This study employs a randomised controlled non-inferiority design determining if the single SWI technique is non-inferior to the four SWI technique more commonly used in clinical practice. This research gap was identified in the literature.

The project has the potential to make a significant contribution to maternity and midwifery research and patient care. Nationally and internationally, maternity care is offered in a diverse range of settings and models of care, offering different services and options in terms of pain management. Many women may not have access to narcotics and epidural analgesia, or these forms of analegisia may be unacceptable due to actual or perceived side effects or cultural considerations. The implementation of a best practice, evidenced based SWI technique for the relief of back pain in labour will provide an alternative analgesic option that addresses consumer demand for low intervention strategies. The procedure is not technology dependent, relatively simple, and may be an effective and feasible analgesic strategy suitable for any maternity care setting or model. Therefore, this trial will make a significant contribution to the evidence supporting the most effective administration of SWI. Important clinical (e.g. increased women's satisfaction/acceptability of SWI administration) and cost benefits (e.g. reduced staff/time required for administration) might be expected if the analgesic efficacy of the single needle technique can be shown to be no less effective than the four injection method.

